### Participant timeline

Participant’s timeline through the trial is presented in
Figure 1.

**Figure 1. f1:**
[figure not shown]
Participant flow diagram through YOGA-D pilot randomized trial.

### Sample size

We plan to recruit around 25 pregnant women with depression in each arm (total=50). This is based on the recommended sample size for pilot randomized controlled trials by Whitehead
*et al.* According to the authors, a sample size of 25 in each arm is adequate for a small standardized effect size (0.2) between the two arms
^
35
^. Assuming a conservative prevalence of 10% for antenatal depression and a 15% non-response rate, we plan to screen around 600 pregnant women.

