## Introduction

### Background

Depression can affect women either during pregnancy (antenatal depression) or after the delivery (postnatal depression). Maternal depression is a serious public health problem and is associated with negative health outcomes both in women and their offsprings. In high-income countries, 7% to 15% women experience antenatal depression, in low-income and middle-income countries the prevalence of antenatal depression is higher (19–25%)
^
1
^. One in four women in South Asia is likely to experience depression during pregnancy, while in India, the pooled prevalence of antenatal depression is 17.7% (95% CI: 11.2%–26.9%)
^
2
^.

Antenatal depression is associated with higher risk of pregnancy-related mortality and morbidity, pre-term delivery, low birth-weight, post-partum depression and adverse neuro-cognitive developmental outcomes in infants, children and adolescents
^
1
^. Anti-depressant medications in pregnancy are associated with fetal exposure risk
^
3
^ and Cognitive Behavior Therapy based interventions are not yet scaled up due to several implementation barriers resulting in poor access to mental health care during pregnancy, especially in low resource settings
^
4,
5
^. To improve ‘access’ to care, there is a critical need to identify interventions that can be practiced by women as ‘self-care’, are culturally ‘acceptable’ to them, less resource-intensive and most importantly are ‘effective’ in treating antenatal depression.

Prenatal Yoga, a form of Yoga tailored to be safe, gentle, and helpful for pregnant women, represents a promising strategy for the prevention and treatment of antenatal depression in different settings across the globe. The findings of meta-analyses suggest that Yoga-based interventions are a promising non-pharmacological modality for the management of antenatal depression, and the overall safety, accessibility and low cost make it an appealing public health intervention
^
6,
7
^.

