### Eligibility criteria

We will first enlist all pregnant women in the study villages with the help of Anganwadi workers. We will invite these women to a small group meeting in the Anganwadi centers to explain the proposed study.
Anganwadi is a community-based center providing healthcare check-up and referral health services, supplementary nutrition, immunization, and non-formal pre-school education. Expectant and nursing mothers, children, and adolescent girls are the primary beneficiaries. These centers were established as part of the Integrated Child Development Service (ICDS) and are managed by female community health workers called Anganwadi workers. Each center caters to a population of approximately 1000 people in rural areas. Anganwadi workers have an updated list of all pregnant women in their respective areas.

Similarly, trained Research Assistants (RAs) will approach pregnant women attending the antenatal clinic of the PIMS (and private antenatal clinics) and brief them about the proposed study. RAs will then screen and complete an eligibility assessment form for women who agree to participate in the study.

The inclusion/exclusion criteria are as follows:

**
*Inclusion criteria:*
**

-Adult pregnant women above 18 years of age-Gestational age between 12–26 weeks-Singleton pregnancy-Patient Health Questionnaire-9 (PHQ-9) score of 10 or more-Planning to stay in the study area (villages and towns described above) throughout study duration (approximately four months)

**
*Exclusion criteria:*
**

-Pregnant women advised rest/restriction of physical activities/laborious tasks by their obstetrician due to medical/obstetric problems-History of one or more spontaneous abortions-History of cervical stitch/cerclage operation-History of pre-term labor/premature rupture of members-Receiving treatment for depression or any other mental health condition-Presence of death wish/ suicidal thoughts almost every day (score of 3 on PHQ9 item 9)-History of hypertension, heart disease, diabetes (including gestational diabetes), respiratory disease, severe anemia, lower respiratory tract infection-Inability to communicate in Marathi language-Inability to attend in-person yoga sessions

Participants who completed the eligibility assessment but did not fulfill all the inclusion criteria will receive educational leaflets about physical activity, sleep, and diet during pregnancy.

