### Recruitment

Participants will first complete the informed consent procedure; the baseline assessment will follow this. RAs will administer the structured questionnaire before the randomization. The structured questionnaire will include data on demographic and socio-economic measures and primary and secondary outcome measures. Informed consent procedure and baseline assessment will take place in the community setting (Anganwadi or a public health facility) or antenatal clinic of PIMS. Participants eligible for trial enrollment will be requested to come to the community/health center closest to their homes in about a week for randomization. IC will randomize the participants in the community/health center, and he/she will work independently of RAs who will not be aware about the treatment allocation.

It is likely that some women may wish to practice yoga and may not be ready for randomization, while some may also wish to practice yoga, but their PHQ-9 score is less than 10. We will offer them an alternative to be part of a cohort and provide the Yoga-Sanskar intervention. We will follow them similarly to the trial participants and complete the three-month and post-delivery outcome assessments.

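### At the stated 10% prevalence, screening 600 leaves one woman to cover all exclusions and refusals; and 25 per arm should not be called adequate for an effect of 0.2

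*Protocol article*

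**What the plan says.** The Sample size section sets a target of about 25 women with depression per arm, 50 in all. It gives the basis as "This is based on the recommended sample size for pilot randomized controlled trials" and reports from the cited source that "a sample size of 25 in each arm is adequate for a small standardized effect size (0.2) between the two arms". No significance level, power or test is named. The screening number comes next: "Assuming a conservative prevalence of 10% for antenatal depression and a 15% non-response rate, we plan to screen around 600 pregnant women". The section does not define non-response.

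Other sections describe further losses between a positive screen and randomisation:

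- **Eligibility criteria.** Depression for entry means "Patient Health Questionnaire-9 (PHQ-9) score of 10 or more". Nine exclusion criteria then apply, for example "History of one or more spontaneous abortions", current treatment for a mental health condition, and inability to attend in-person sessions. Women must also have a singleton pregnancy, be within the gestational window and plan to stay in the area.
- **Recruitment.** "It is likely that some women may wish to practice yoga and may not be ready for randomization". These women are offered the yoga intervention in a non-randomised cohort. Eligible women are asked to come back about a week after baseline to be randomised.

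The Background gives a pooled antenatal depression prevalence for India of 17.7%, with a 95% confidence interval of 11.2% to 26.9%.

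**The concern.** The screening number allows for prevalence and one undefined non-response rate. Neither the exclusion criteria nor the refusals that the protocol expects enter the calculation. Eligibility and recruitment rates are part of the first primary objective. If fewer than 50 women are randomised from 600, a reader cannot tell whether the trial is hard to recruit to or the target left out a planning step.

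The sentence on the effect of 0.2 has a different problem. It does not say what 25 per arm is adequate for, and its natural reading is that a difference of 0.2 SD between the arms can be detected or estimated usefully. Preliminary efficacy on depression is also listed under the primary objectives, so that reading could make a null result look more informative than it is.

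**Working it through.** **Inputs.** From Sample size: 50 randomised, 25 per arm, prevalence 10%, non-response 15%, about 600 screened, standardised effect 0.2. From Background: prevalence 17.7% (11.2% to 26.9%). Assumed here, because the documents give no value: further loss of 20% to 40% among PHQ-9-positive responders (exclusion, refusal or no return), two-sided alpha 0.05, and baseline-to-follow-up correlations of 0.3 to 0.7.

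**1. The stated figure.** Number to screen = 50 / (prevalence x (1 - non-response)) = 50 / (0.10 x 0.85) = 588.2. This agrees with about 600.

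**2. The yield at the stated inputs.** 600 x 0.10 x 0.85 = 51. The tolerated further loss is 1 - 50/51 = 2.0%, or one woman.

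**3. Other readings of the 15%.**
- If it means refusal among depressed women, 600 x 0.10 = 60 and 60 x 0.85 = 51. Refusal is then covered, but one woman still has to cover all exclusions.
- If it means loss to follow-up, 60 women would be randomised, which does not match a total of 50, and exclusions are still not covered.

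No reading covers exclusion, refusal and non-return together.

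**4. Dependence on prevalence.** Tolerated loss = 1 - 50 / (600 x prevalence x 0.85).

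| Prevalence | PHQ-positive responders from 600 | Tolerated loss |
|---|---|---|
| 10% (Sample size) | 51.0 | 2% |
| 11.2% (lower limit) | 57.1 | 12% |
| 17.7% (pooled) | 90.3 | 45% |
| 26.9% (upper limit) | 137.2 | 64% |

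**5. Number to screen for 50, and yield from 600, under assumed further loss.** Number = 50 / (prevalence x 0.85 x (1 - loss)), rounded up.

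| Loss | 10%: screen (yield from 600) | 17.7%: screen (yield from 600) |
|---|---|---|
| 20% | 736 (41) | 416 (72) |
| 30% | 841 (36) | 475 (63) |
| 40% | 981 (31) | 554 (54) |

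Turned round, 600 gives 50 when prevalence is at least 50 / (600 x 0.85 x (1 - loss)). That is 50 / 408 = 12.3% at 20% loss and 50 / 306 = 16.3% at 40% loss.

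**6. What 25 per arm gives for an effect of 0.2 SD.**
- Power: the noncentrality is 0.2 x sqrt(25/2) = 0.707. With 48 degrees of freedom and two-sided 0.05, power is 10.7% (10.5% by the normal approximation).
- Power with baseline adjustment: 11% to 17% at correlations of 0.3 to 0.7.
- Size for 80% power: 2 x (1.960 + 0.842)^2 / 0.2^2, giving 393 per arm.
- Precision, unadjusted: the 95% half-width is 2.011 x sqrt(2/25) = 0.57 SD.
- Precision, adjusted: multiplying by sqrt(1 - r^2) gives 0.57 x 0.954 = 0.54 SD at r = 0.3 and 0.57 x 0.714 = 0.41 SD at r = 0.7.

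Even the narrowest of these intervals extends about twice the named effect on each side of the estimate.

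**The case against.** The case for leaving the text alone has real force.

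- **The 600 reproduces.** A reader might infer that it is miscalculated, or that it cannot give 50 on its own assumptions. The documents do not support either: on its two inputs it gives 51.
- **The margin may lie in the prevalence.** The protocol calls 10% conservative, and it is below the lower confidence limit in the Background. At 17.7%, 600 is enough even with 40% further loss. This stands as a reason not to predict failure. However, the article does not say that the gap is meant to cover exclusions and refusals. It also does not say which instrument or cut-off lies behind 17.7%, whereas entry requires a PHQ-9 score of at least 10.
- **The loss rates are not in the documents.** The 20% to 40% is an assumption, so the shortfalls in step 5 illustrate the point and do not forecast recruitment. Step 2 needs none of them.
- **Screening is not capped.** The numbers are approximate, there are several recruitment sources, and the article sets no threshold for failed recruitment. A reader might infer that recruitment will fail; the documents do not show that.
- **No power is claimed for 0.2.** A reader might infer that the trial is offered as powered for 0.2, or should be. The section reports a recommendation for pilot size and states no alpha, power or test, and the aim is preliminary efficacy. What the cited source means by adequate cannot be checked here. The fault is therefore one of wording: as printed, the sentence gives 25 per arm a property it lacks for both detection and estimation.

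**Conclusion.** The point holds as an omitted step and a wording fault. At the protocol's own 10% and 15%, the screening target has a margin of one woman in 51, although the protocol itself lists nine exclusions, expects some refusal of randomisation and requires a return visit. This needs no outside assumption. Whether 600 is enough in practice is open: it fails at 10% prevalence with any loss above about 2%, and holds at 17.7% up to about 45%.

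On the second part, 25 per arm is a defensible pilot size, but it is not informative about a difference of 0.2 SD. Power is about 11%, and the unadjusted half-width is 0.57 SD (0.41 to 0.54 SD with baseline adjustment at the assumed correlations). These figures assume 25 analysed per arm and two-sided 0.05. Neither part undermines the design. Both affect how recruitment and a null efficacy result will be read.

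**What to change.** 1. Define the 15%: non-response to screening, refusal to take part, or loss to follow-up.
2. Add an explicit eligibility-and-consent fraction among PHQ-9-positive women, shown as a range. Then either restate the target (for assumed further losses of 20% to 40%, about 736 to 981 at 10% prevalence or 416 to 554 at 17.7%), or keep 600 and state the prevalence and loss at which it gives 50 (about 12.3% prevalence with 20% loss, 16.3% with 40%).
3. Replace the sentence on 0.2. Say that 25 per arm is a pilot size chosen to estimate feasibility rates and outcome variability, that it gives a 95% half-width of about 0.57 SD for an unadjusted PHQ-9 difference (narrower with baseline adjustment, with the assumed correlation stated), and that it is not meant to detect or rule out an effect of 0.2.

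The cost is a few sentences. No extra women are randomised and the analysis does not change. The only downside is that the stated screening target may rise.

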### Recruitment

Participants will first complete the informed consent procedure; the baseline assessment will follow this. RAs will administer the structured questionnaire before the randomization. The structured questionnaire will include data on demographic and socio-economic measures and primary and secondary outcome measures. Informed consent procedure and baseline assessment will take place in the community setting (Anganwadi or a public health facility) or antenatal clinic of PIMS. Participants eligible for trial enrollment will be requested to come to the community/health center closest to their homes in about a week for randomization. IC will randomize the participants in the community/health center, and he/she will work independently of RAs who will not be aware about the treatment allocation.

It is likely that some women may wish to practice yoga and may not be ready for randomization, while some may also wish to practice yoga, but their PHQ-9 score is less than 10. We will offer them an alternative to be part of a cohort and provide the Yoga-Sanskar intervention. We will follow them similarly to the trial participants and complete the three-month and post-delivery outcome assessments.

### Assignment of interventions: allocation

**
*Sequence generation*
**

Serially numbered, opaque, sealed envelopes (SNOSE) will be used for treatment allocation. Clinical Research Coordinator (CRC) based in the Directorate of Research, PIMS will prepare SNOSE using the randomization list created by the trial statistician who will independently generate the randomization list using the statistical program
R (version 3.6.1). First, a list of variable block sizes (randomly selected block sizes of 2/4/6/8) will be created, followed by a list of intervention allocation (YS or EUC) using a 1:1 allocation ratio. CRC and trial statistician will be independent of the study team and will not interact with the RAs or the IC.

**
*Allocation concealment mechanism*
**

The IC will randomly allocate participants to the intervention group using SNOSE after they complete their baseline assessment.

**
*Implementation*
**

The IC will collect a set of opaque sealed envelopes from CRC as per the serial numbers a few hours before the recruitment. The IC will open the opaque sealed envelopes (as per the serial numbers) in front of the participants and immediately inform them about the intervention group (i.e., YS or EUC) assigned to them. Participants will be asked to keep their group assignment private from the RAs at the three-month follow-up, and post-delivery assessments. To maintain allocation concealment, neither the RAs nor any staff working at the hospital will have access to the randomization lists. The IC will inform the CRC of the unique identification number of the participant (and no other details) and the intervention allocation group. The CRC will maintain the record of intervention allocation.

### Assignment of interventions: blinding

**
*Who will be blinded?*
**

Participants, their family members, and study team members involved with intervention delivery (IC and yoga instructors) will be aware of participants’ assigned intervention during the trial. It is not possible to avoid bias arising due to this. RAs will complete baseline, three-month follow-up, and post-delivery assessments, and they will not interact in any way with the intervention team. RAs will not be aware of the intervention allocation status. Participants and family members will be instructed not to disclose whether they are receiving YS intervention or EUC to the RAs at the time of the follow-up assessments. Additionally, RAs will also remind participants not to reveal their group assignment to them so that they remain blind to the participant’s treatment allocation.

Obstetricians will not be aware of the intervention allocation status, minimizing the risk of any change in their behavior while dealing with the participants.

The intervention team led by the IC and the outcome assessment team comprising RAs will not have any interactions during the trial. They will work independently of each other in separate locations and will have no communication about trial participants and their intervention allocation status. During the training of RAs in the outcome assessment team, particular emphasis will be given to explaining the equipoise between the two interventions.

We will monitor the risk of contamination at the level of the yoga instructors, intervention coordinator, and participants. Yoga instructors and the intervention coordinator will be requested not to share the information about YS with pregnant women other than those enrolled in the intervention arm. They will also ensure that participants in both the arms adhere to the group randomly allocated to them.

**
*Procedure for unblinding if needed*
**

If there is any yoga-related adverse event, we will reveal the intervention group allocation to the obstetrician.

### Data collection and management

**
*Plans for assessment and collection of outcomes*
**

Research Assistants (RAs) will utilize Case Record Forms (CRF) to gather information during the initial assessment and the three-month follow-up. Data collection will be conducted using pen and paper, with subsequent manual entry into Microsoft Excel for digital conversion. The data will be stored as a CSV file, with original timestamps for entries and a record of any subsequent modifications in an audit trail. Documentation concerning the fidelity and quality of yoga intervention delivery will follow a similar process, with data stored in CSV format. Qualitative data will be recorded using digital voice recorders, and accompanying memos and field notes will be transcribed from Marathi to English for analysis. Data will be anonymized but associated with the trial ID.

The Clinical Research Coordinator (CRC) will conduct weekly checks on each data source for accuracy, consistency, and completeness, promptly addressing any queries and updating the database while maintaining an audit trail. Initially, separate databases will house distinct data types, with consolidation into a master database upon completion of data collection. Password protection will safeguard the data, with exclusive access granted to the CRC and no other trial team members.

**
*Plans to promote participant retention and complete follow-up*
**

During the initial assessment, RAs will inform the participants about the date for the three-month follow-up evaluation. RAs will call the participants one week before the follow-up assessment to remind them about the assessment. If the participant is traveling or is unavailable for any reason, there will be a seven-day window following the due date to complete the assessment. The assessments will be conducted preferably at the health center or Anganwadi center. If the participant is unable to come there, then the RA will complete the assessment at participant’s home.

**
*Data management*
**

We will prepare a Trial Master File that will encompass all vital documents. Documentation pertinent to the trial will be preserved for seven years following its conclusion. After this period, paper-based data will be securely disposed of, while electronic data will be purged of identifiable information.

All Case Record Forms (CRFs) and associated study documents will be securely housed within the Directorate of Research, PIMS. Password-protected servers will safeguard electronic records. We will use coded identification numbers to identify data, ensuring participant confidentiality. Participant information in physical form will be stored securely in locked cabinets. We will utilize anonymized data to analyze and disseminate results at conferences and through academic publications.

**
*Confidentiality*
**

The identity and privacy of research participants will be protected. Any variable that may help infer the identity of any participant will be deleted from the database.

### Statistical methods

We will first compute the descriptive statistics for demographic, socio-economic, pregnancy-related characteristics, and outcome measures for all the trial participants in both arms. Descriptive statistics will include means and standard deviations (for continuous variables) or proportions (for discrete variables). We will use a t-test and chi-square test to compare means and proportions, respectively, to estimate the difference in the baseline characteristics between the two arms. We will use the intention-to-treat analysis to assess preliminary efficacy, binomial regression models to estimate risk ratios and 95% confidence intervals for binary outcomes and linear regression models to estimate regression coefficients for continuous outcomes. Analyses of continuous outcomes will additionally adjust for the baseline value of that outcome and any imbalances of baseline values of key covariates. The trial statistician will conduct the statistical analyses in
Stata version 18.

**
*Methods for additional analyses (e.g., subgroup analyses)*
**

*Process evaluation analysis*

We will audio-record all the in-depth interviews (IDIs) and focus group discussions and maintain field notes. Interviews in English will be transcribed verbatim, while those conducted in Marathi will be transcribed and translated into English. Team members proficient in both English and Marathi will conduct back-translation checks. Qualitative data will undergo analysis using the content analysis method. An initial coding framework comprising overarching themes will be established a priori. Subsequent themes will emerge from the data through inductive reasoning. NVivo 9 software (QSR) will facilitate data coding. The Principal Investigator will primarily oversee data analysis and synthesis of findings.

**
*Methods in analysis to handle protocol non-adherence and any statistical methods to handle missing data*
**

Complier Average Causal Effect (CACE) analysis will be carried out to assess the effect of receiving treatment as defined in the protocol. CACE will be done in two ways. Full compliance is defined as attendance at the first five sessions and completing all the competency assessments. The first type of analysis will involve fully compliant participants. In the second type of analysis, participants with any compliance (attendance at one yoga session or more) will be included. The extent and pattern of missing data for each outcome will be explored. Multiple imputation of missing values will be performed if there are more than 10% missing values at endpoint.

**
*Plans to give access to the full protocol, participant level data and statistical code*
**

The trial protocol will be submitted to an open access journal before the initiation of participant enrollment. Additionally, the trial protocol and the supplementary files will also be uploaded on a dedicated website:

https://rahulshidhayelab.in/YOGA_D/

Six months after the completion of the trial, data will be uploaded on an open access data repository (e.g., Figshare) along with the statistical code used for the analysis.

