### Objectives

The overall aim of this pilot randomized controlled trial is to examine the feasibility, acceptability, and preliminary efficacy of Yoga-Sanskar (YS), a yoga-based intervention to improve antenatal depression.

The primary objectives of this pilot randomized trial are:

1. To estimate participant eligibility, recruitment and retention-in-care and study completion rates.

2. To assess the feasibility of delivering Yoga-Sanskar intervention and acceptability of this intervention by the participants.

3. To assess the adherence rate, safety, and preliminary efficacy of Yoga-Sanskar intervention in improving antenatal depression (primary outcome).

The secondary objectives of this pilot randomized trial are:

1. To assess the preliminary efficacy of Yoga-Sanskar intervention on anxiety, stress, and quality of life (secondary outcomes) during pregnancy.

2. To assess the preliminary efficacy of the intervention on pregnancy outcomes (preterm labor, type of delivery, birthweight, and post-partum depression.

3. To explore the feasibility of administering all the evaluation tools including the Client Service Receipt Inventory to assess the healthcare and intervention costs.

4. To explore the feasibility of following up recruited participants four weeks post-delivery.

5. To study the psychometric properties of the translated versions of the Pregnancy Experience Scale, Common Symptoms in Pregnancy inventory, Attitude towards Yoga during Pregnancy scale, and the Five Facet Mindfulness Questionnaire.

**
*Trial design*
**

Single-blind individual randomized parallel group-controlled pilot trial with 1:1 allocation ratio.

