Improvement in self-awareness/mindfulness is proposed as a potential mechanism of action through which a yoga-based intervention improves mental health outcomes/depression
^
13
^. The training during yoga sessions will focus on improving self-awareness/mindfulness, as the increase in mindfulness is associated with decreased distress and other psychological symptoms. We will use a 17-item Five-Facet Mindfulness Questionnaire that measures five aspects: non-reactivity to inner experience, observing, acting with awareness, describing with words, and non-judging of experience. The original English version of the scale
^
34
^ is translated into Marathi and is included in the supplementary file (
*Extended Data*
^
17
^).

**
*Pregnancy outcomes*
**

We will gather information about the outcome of pregnancy (normal birth/stillbirth), whether the delivery took place at-term, and the birthweight of newborn based on the hospital records.

**
*Self-report log*
**

Participants in both arms will document any injuries or non-serious adverse events during the trial in the yoga journal (and a similar journal will be given to the participants in the EUC arm). IC and
*Sahayoginis* will keep track of this and report to the CRC in case of adverse events.

**
*Economic evaluation*
**

In the future explanatory trial, we plan to assess the cost-effectiveness of the YS intervention relative to the EUC. Effectiveness/health outcomes will be estimated using the Quality Adjusted Life Years based on the EQ-5D-5L data collected at the baseline and three months post-randomization. Costs will comprise intervention costs, healthcare resource costs, and wage loss costs. In this pilot trial, we will explore the feasibility of using the Client Service Receipt Inventory to estimate healthcare resource costs and wage loss costs. Intervention costs will be estimated using the trial records.

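### The risk-ratio regression planned for binary outcomes may give no usable estimate for preterm birth at about 25 women per arm; a risk difference should be prespecified for it (minor)

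*Protocol article*

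**What the plan says.** In the protocol article, Statistical methods prescribes intention-to-treat analysis for preliminary efficacy and, within it, "binomial regression models to estimate risk ratios and 95% confidence intervals for binary outcomes". Linear regression is named for continuous outcomes. The section draws no distinction between common and rare binary outcomes.

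Secondary objective 2 (Objectives) is "To assess the preliminary efficacy of the intervention on pregnancy outcomes (preterm labor, type of delivery, birthweight, and post-partum depression". Under Outcomes, the paragraph on pregnancy outcomes says that the team will collect "outcome of pregnancy (normal birth/stillbirth), whether the delivery took place at-term, and the birthweight of newborn based on the hospital records". Preterm birth is therefore a binary outcome with an efficacy objective. Stillbirth is collected but is not listed in that objective.

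Sample size: "We plan to recruit around 25 pregnant women with depression in each arm (total=50". The Eligibility criteria remove women at raised obstetric risk, for example those with "History of pre-term labor/premature rupture of members", and also those with earlier spontaneous abortion, cerclage, hypertension, heart disease or diabetes. They also require a PHQ-9 score of at least 10. The article gives no expected rate for preterm birth or stillbirth.

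**The concern.** A risk ratio from a log-link binomial model needs at least one event in each arm. With an empty arm the log risk ratio runs off to plus or minus infinity. With two empty arms the ratio is undefined. Software may still print a coefficient and report convergence, but the interval means nothing.

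Arms of about 25 leave room for this when the outcome is uncommon, and it becomes more likely if the intervention lowers the event rate. The analyst would then have to pick a replacement after seeing the table. What is at stake is the preterm-birth part of secondary objective 2. The feasibility measures and the PHQ-9 analysis are untouched.

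**Working it through.** **Plan's own figure.** The article states: "Assuming a conservative prevalence of 10% for antenatal depression and a 15% non-response rate, we plan to screen around 600 pregnant women". Check: 50 / (0.10 × 0.85) = 588, and in reverse 600 × 0.10 × 0.85 = 51. The target of 50 women is consistent with the screening plan, and "Single-blind individual randomized parallel group-controlled pilot trial with 1:1 allocation ratio" gives n = 25 per arm.

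**Inputs**
- n = 25 per arm: Sample size section.
- Preterm rate p: not given. Assumed 5% to 15%.
- Stillbirth rate: not given. Assumed 0.5% to 3%.
- Halving of the rate by the intervention: an assumption, for illustration only.

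**Formulas**
- No event in one arm: q = (1 − p)^25.
- At least one arm empty, equal rates: 1 − (1 − q)².
- At least one arm empty, rate halved in one arm: 1 − (1 − q)(1 − h), with h = (1 − p/2)^25.

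**Preterm birth, with a commoner outcome for comparison**

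| Assumed rate p | q | At least one arm empty, equal rates | At least one arm empty, rate halved |
|---|---|---|---|
| 5% | 0.277 | 48% | 66% |
| 8% | 0.124 | 23% | 44% |
| 10% | 0.072 | 14% | 33% |
| 15% | 0.017 | 3% | 16% |
| 20% | 0.004 | 0.8% | 8% |

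Worked line at 10%: 0.90^25 = 0.072, so 1 − 0.928² = 0.138. With 5% in the other arm, 0.95^25 = 0.277 and 1 − 0.928 × 0.723 = 0.329.

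With 21 per arm (15% loss, an assumption) and equal rates, the probabilities at 5%, 10% and 15% are 57%, 21% and 6.5%.

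**Stillbirth, if compared by the same regression (equal rates, 25 per arm)**

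| Assumed rate | At least one arm empty |
|---|---|
| 3% | 72% |
| 2% | 84% |
| 1% | 95% |
| 0.5% | 99% |

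**What the regression returns.** A log-binomial model was fitted to 25 v 25 tables.
- 0 v 3 events: log risk ratio about −21, standard error about 14,500. Both values only reflect where the iteration stops; the true limit is minus infinity. The fit was still flagged as converged.
- 3 v 0 events: the mirror image.
- 0 v 0 events: no information on the ratio.
- 1 v 3 events: finite, log risk ratio −1.10, standard error 1.12.

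**When the ratio exists.** 2/25 v 3/25 gives a risk ratio of 0.67. The standard error of its log is √(1/2 − 1/25 + 1/3 − 1/25) = 0.868, so the 95% interval is 0.12 to 3.65.

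**Risk difference, Newcombe 95% interval**
- 0/25 v 3/25: the Wilson limits are 0 to 0.133 and 0.042 to 0.300. The difference is −12.0 points. Lower limit: −0.120 − (0.300 − 0.120) = −0.300. Upper limit: −0.120 + √(0.133² + (0.120 − 0.042)²) = +0.035.
- 0/25 v 0/25: difference 0, interval −13.3 to +13.3 points.

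The difference and its interval are defined in every table.

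**The case against.** The strongest reply is that a rule for empty cells is ordinarily left to the analysis plan, which is not shown, so its absence from a condensed article is no error. As far as it concerns a missing detail, that is right. What remains is a method that the article does state, without exception, for an outcome in its own objective, and that can fail at its own sample size.

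The other replies limit the point:
- **How often.** A reader might infer that the planned estimate will usually be lost. The documents give no rate, and for preterm birth under equal rates the probability is near one half only at about 5%.
- **Direction of the rate.** The obstetric exclusions may lower it. But every randomized woman has a PHQ-9 score of 10 or more, and the Abstract and Background associate antenatal depression with preterm labor or delivery. The net effect is unknown.
- **Stillbirth and serious adverse events.** It is tempting to lead with the near-certain failure for stillbirth. Yet stillbirth is not in the efficacy objective, and the article treats it as a reason for discontinuation and as a serious adverse event. No section plans a risk ratio for serious adverse events.
- **Existence of a ratio interval.** The article does not specify a Wald interval. For 0/25 v 3/25 the point estimate is 0, and a score interval for the ratio runs from 0 to about 1.2. So the failure belongs to the regression coefficient and its usual interval; only 0 v 0 leaves the ratio itself undefined.
- **Descriptive results.** Proportions per arm are already promised, so the real addition is a between-arm measure that is always defined.

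**Conclusion.** The point holds in a limited form. For preterm birth, the stated regression gives no finite coefficient and no usable Wald interval in 48% of trials at an assumed rate of 5%, 14% at 10% and 3% at 15%, with equal rates and 25 per arm. If the intervention halves the rate, the range over 5% to 15% is 66% to 16%. For stillbirth the failure is the expected outcome, but only if it is compared in this way at all. All these figures rest on assumed event rates and on full follow-up; loss to follow-up raises them.

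The documents do not support extending this to binary outcomes in general: at 20% or more with equal rates the probability is below 1%. Importance is minor, because one component of a secondary objective in a pilot is affected and efficacy is described as preliminary throughout.

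**What to change.** Add to Statistical methods: for preterm birth, and for stillbirth if the arms are compared on it, report the number and proportion of events per arm and the risk difference with its Newcombe 95% interval. Give the binomial-regression risk ratio in addition only when both arms have at least one event. State that these results are descriptive in the pilot. Keep the risk ratio as planned for the commoner binary outcomes. No minimum total number of events and no extension to serious adverse events is needed.

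The cost is one or two sentences, with no new data and no change to the sample size. The downside is that rare outcomes will appear mainly on the difference scale, which is less convenient for readers who want a ratio.
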